### Sample size

Pilot RCTs do not test efficacy, and formal sample size calculations are not typically used. However, if too small, a pilot study may underestimate the standard deviation leading to underpowered efficacy RCTs. Sim et al. [30] suggested that the sample size of a pilot study be determined based on the desired level of confidence for the standard deviation of the primary outcome measure in the larger-scale RCT, and the power and significance level anticipated. Additionally, attempts to minimize the total sample size required should be made. Given an expected 10% loss to follow-up, and to maintain equal group sizes, the proposed pilot sample size will be *n* = 46. This is adequate to assess recruitment success and feasibility issues and provides sufficient data for exploratory analysis of the secondary outcomes.

### Randomization and blinding

Participants will be randomized to either the active tDCS or sham tDCS treatment condition in a 1:1 allocation ratio. An independent research assistant will prepare a randomization schedule using random permuted blocks of varying sizes to ensure allocation concealment and will assign participants to active or sham tDCS groups. Block sizes and variations will only be known to the independent research assistant. The allocation sequence will be entered into a password-protected Excel sheet. A separate, blinded member of the study team will enroll participants. Participants, family members, assessors, and investigators will all be blinded to group allocation. The devices will be preprogrammed with codes that correspond to specific stimulation parameters. During each session, participants will be provided with a code aligning with their group assignment to maintain blinding. Unblinding of participants will be permissible if the participant is no longer participating in study procedures and requires information on group allocation for medical purposes. In this case, the principal study investigator will reveal group membership to the participant. To minimize observer bias, the principal investigator will not be involved in data collection or analysis.

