A summary of the study schedule is shown in Fig. 1. All in-person assessments will be conducted at Holland Bloorview Kids Rehabilitation Hospital in Toronto, Canada. The take-home tDCS device will be provided at the first baseline assessment visit (T0). The participant and/or caregiver will be trained on administration and device use by a study team member. The study team member will demonstrate how to use the device on the participant in a step-by-step manner. Following the demonstration, the caregiver or participant will attempt to recreate the demonstration, and the study team member will observe to ensure they are following the steps correctly and assist with any questions or concerns. The following week, participants will begin home-based tDCS treatment sessions. Fifteen sessions will be conducted over 3 weeks (5 days/week, Monday–Friday), with remote support from the study team via videoconferencing [42, 44]. Each session will be 30 min in duration, including a 5-min intake and equipment set-up, 20-min tDCS, and 5-min debrief and observation to ensure there are no unanticipated adverse events [34, 45]. Previous studies have shown that 15 sessions of 20-min tDCS at 2 mA may be effective in this population for a variety of behaviors [18, 46].

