#### Feasibility

Feasibility measures include recruitment rate, retention rate, adherence rate, and success of randomization and blinding. Recruitment and attrition will be calculated using the electronic audit trail generated by the documentation kept by the independent RA and statistician and research assistant. Adherence will be calculated based on the number of sessions attended and completed by participants who complete all assessments. The success of blinding will be determined based on responses to the questions “What group do you think you were in?” and “How sure are you?”, which will be asked on the follow-up tolerability questionnaire (adapted from Garvey et al., 2001) [52]. Descriptive statistics will be completed to establish if the comparison and intervention groups are similar in age, gender, ASD severity, and clinical symptom severity. The success of randomization will be determined by evaluating group differences in sex distribution and median age. Randomization will be determined to be successful if the differences in sex distribution are within ± 2 participants, and the median age difference is within ± 2 years.

The feasibility of the optional MRI component will be evaluated based on total and successful attempts at completing the MRI protocol. There is a paucity of data on neural outcomes in this population; therefore, any amount of data collected is valuable. Previous MRI studies examining children with ASD include samples between 20 and 50 participants [53–57]. In a hypothetical sample size, *n* = 100 (*n* = 50 per group) for a full-scale RCT, including data from at least 20 individuals in each group would be sufficient to conduct an analysis. Given this, the optional MRI component of this study will be feasible if ≥ 20% of participants in each group have successful MRIs. A successful attempt is one in which a majority of the scan is completed with minimal motion artifact as determined by the MRI technician.

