### Data analysis

#### Primary measures analysis

##### Feasibility

Feasibility measures will be analyzed as per the progression criteria outlined in Table 1. These criteria were determined based on recommendations by Avery et al. to assess whether to proceed with a full-scale RCT [75]. Associations between participant characteristics (e.g., age, IQ, travel distance) and ability to complete all trial tasks will be examined to inform the planning of a large-scale RCT. *T*-tests will be conducted for associations with continuous variables (e.g., IQ, age, travel distance). Chi-squared tests will be conducted for associations with categorical variables (e.g., gender).

**Table 1 Tab1:** Progression criteria for feasibility metrics

	**GO–proceed with RCT**	**AMEND–proceed with changes**	**STOP–do not proceed unless changes are possible**
Recruitment target	*n* = 46	*n* = 36–45	*n* < 36
Adherence	≥ 90% of tDCS sessions are completed by participants who complete all assessments	70–89% of tDCS sessions are completed by participants who complete all assessments	< 70% of tDCS sessions are completed by participants who complete all assessments
Participant retention	≥ 90% retention	80–89% retention	< 80% retention
Optional MRI target	≥ 20% of participants have successful MRIs in each group	10–19% of participants have successful MRIs in each group	< 10% of participants have successful MRIs in each group

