##### Neural

Structural and functional neuroimaging changes between timepoints T0, T1, and T2 will be compared between groups, and associations between baseline neuroimaging and treatment outcomes will be explored. Freesurfer (https://surfer.nmr.mgh.harvard.edu/) will be used to obtain cortical thickness from structural MRI data. MRtrix3 software will be used to process diffusion imaging data to determine changes in white matter tracts [76]. Blood-oxygen-level-dependent (BOLD) signal of resting-state functional MRI will be analyzed using the fMRIPrep pipeline. All results will be corrected for multiple comparisons using the false discovery rate (FDR) method (*P*_FDR_ < 0.05). Changes in network activity will be analyzed using the left DLPFC as a seed.

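### MRI feasibility is judged separately in each arm, but the allocation list names no MRI stratum, so near the threshold the GO or AMEND result depends partly on chance

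*Protocol article*

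**What the plan says.** Under Randomization and blinding, the article sets a 1:1 ratio ("Participants will be randomized to either the active tDCS or sham tDCS treatment condition in a 1:1 allocation ratio") and describes the list: "An independent research assistant will prepare a randomization schedule using random permuted blocks of varying sizes to ensure allocation concealment". Block sizes are concealed. No stratification factor is named, for MRI or anything else.

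The Sample size section gives the total: "to maintain equal group sizes, the proposed pilot sample size will be *n* = 46". That is 23 per arm.

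The Feasibility section under Primary outcome measures sets the MRI rule by arm: "the optional MRI component of this study will be feasible if ≥ 20% of participants in each group have successful MRIs". Table 1 repeats it as the GO criterion ("≥ 20% of participants have successful MRIs in each group") and sets AMEND at "10–19% of participants have successful MRIs in each group". STOP is below 10%. None of the other Table 1 criteria is worded by group.

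MRI is optional and is first done at T0. On treatment timing, the tDCS intervention section says "The following week, participants will begin home-based tDCS treatment sessions". The Neural analysis section says "Structural and functional neuroimaging changes between timepoints T0, T1, and T2 will be compared between groups".

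**The concern.** Opting in to MRI is a family's choice, and the first scan comes before any stimulation. How the opt-in children divide between active and sham says little about whether scanning is feasible. A by-arm rule with no matching balance in the allocation lets that division move the progression band. The pilot could record AMEND with an overall success rate above 20% simply because the few scanned children fell unevenly. The exploratory neural comparison would also rest on unequal arms.

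**Working it through.** **Inputs from the article.** 46 children, 1:1, so 23 per arm. GO at 20% or more in each arm; AMEND 10–19%; STOP below 10%.

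**Counts per arm.** 0.20 × 23 = 4.6, so GO needs 5 (4/23 = 17.4%, 5/23 = 21.7%). AMEND is 3 or 4 (13.0%, 17.4%). STOP is 2 or fewer (2/23 = 8.7%). GO overall needs at least 10 successes (10/46 = 21.7%); with 9 it cannot be reached.

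**Assumption.** The number M of successful children overall is not given, so a range is shown. All 46 are in the denominator, and MRI success is taken as unaffected by arm.

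**Formula.** P(k of the M fall in the active arm) = C(23,k) × C(23,M−k) / C(46,M). GO requires k ≥ 5 and M−k ≥ 5.

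- M = 10: only 5:5 passes. C(23,5)² / C(46,10) = 33,649² / 4,076,350,421 = 27.8%. Missed: 72.2%.
- M = 11: 2 × 33,649 × 100,947 / 13,340,783,196 = 50.9%. Missed: 49.1%.
- M = 12: (2 × 33,649 × 245,157 + 100,947²) / 38,910,617,655 = 68.6%. Missed: 31.4%.

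| M | Overall rate | GO missed |
|---|---|---|
| 10 | 21.7% | 72% |
| 11 | 23.9% | 49% |
| 12 | 26.1% | 31% |
| 13 | 28.3% | 19% |
| 14 | 30.4% | 11% |
| 16 | 34.8% | 3% |

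Simulating unstratified permuted blocks (sizes 2/4, 4/6 and 4/6/8, 15,000 runs each) gives misses of 72%, 49–50% and 31–32% at M = 10, 11 and 12, so the formula is a good approximation to the blocked list.

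**Which band a miss falls in.** If the lower arm decides, GO/AMEND/STOP is 28/65/7% at M = 10, 51/46/4% at M = 11 and 69/30/2% at M = 12 (rounded). Table 1 does not say how to classify arms that fall in different bands.

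**Sensitivity to the denominator.** With 21 analysed per arm GO still needs 5, and the misses at M = 10, 11 and 12 are 72%, 48% and 31%. The stated 10% loss leaves 0.9 × 46 = 41.4. With arms of 20 and 21, GO needs 4 and 5, and the misses are 48%, 31% and 18%. With 20 per arm GO needs 4, and they are 27%, 16% and 8%.

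**Without fixing M.** Let each child have success probability p, with 23 per arm. The by-arm rule gives GO with probability P(Bin(23,p) ≥ 5)²; the pooled rule gives P(Bin(46,p) ≥ 10). The gap is due to the split alone.

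| p | GO, by arm | GO, pooled |
|---|---|---|
| 20% | 25% | 44% |
| 25% | 51% | 75% |
| 30% | 75% | 92% |
| 40% | 96% | 99.7% |

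**Effect of stratifying (simulated, blocks 2/4 or 4/6).** GO missed at M = 10, 11 and 12:

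- By T0 scan success: 12–19%, 0–1%, 0%.
- By opt-in, 14 assumed to opt in: 58–59%, 21–24%, 2–4%.
- By opt-in, 20 assumed to opt in: 66–67%, 38%, 18%.

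**The threshold itself.** The article derives 20% from needing 20 individuals per group in a trial of 50 per group, but 20/50 = 40%; 20% results only from dividing by the total of 100. At 40%, each arm would need 10 of 23 (9/23 = 39.1%), and the same effect would recur at 20, 21 and 22 successes overall, with misses of 77%, 55% and 38%.

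**The case against.** An unstratified blocked list is an ordinary choice for a 46-child pilot, and the sentence describing it is not wrong in itself. The fragility comes at least as much from applying a by-arm cut-off to 23 children. That stands, and it is why a pooled criterion is offered as an alternative.

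A reader might infer that the pilot will miss the MRI GO band in roughly 30–70% of cases. The article does not support this. Those figures hold only if 10 to 12 children succeed, a window just above the minimum. At a true success rate of 40% the by-arm rule reaches GO in about 96% of trials.

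A reader might also infer that MRI status is wholly settled before treatment, so that the split is pure chance. The article does not say that only the T0 scan counts. It collects MRI at T0, T1 and T2 and judges attempts at the MRI protocol as a whole. If later scans count, success depends partly on retention and tolerance, a by-arm rule has some rationale, and stratifying on the T0 result would not secure it. Nor does the article say when allocation takes place relative to T0.

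The consequence is limited: a miss usually means proceeding with changes, and it concerns an optional component for which the article calls any amount of data valuable. The harm to the neural comparison is slight. An 8:4 split against 6:6 gives (1/8 + 1/4)/(1/6 + 1/6) = 1.125, about 6% in the standard error, and allocation among the scanned children is still random.

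What remains is that a progression rule has to discriminate near its threshold, and there this rule is partly decided by allocation.

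**Conclusion.** The point holds as a minor one. The allocation as described does nothing to balance MRI participation, while the criterion is applied arm by arm. Close to the threshold, the choice between GO and AMEND therefore partly reflects chance. The effect is large at 10 or 11 successes overall and small from about 14. The percentages rest on an assumed number of successes, on the denominator chosen and, for the STOP share, on letting the lower arm decide. That there is no stratum rests on the article naming none; it does not say so outright.

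**What to change.** Do one or both of the following.

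1. Stratify the permuted blocks by MRI opt-in (yes/no), recorded before allocation. If allocation is made after T0 and only the T0 scan defines success, stratify by successful T0 scan instead, which works much better. Opt-in is a partial cure. The cost is two allocation lists in place of one, a short amendment and a possible overall arm imbalance of up to half a block per stratum. Block sizes stay concealed.
2. Judge the MRI GO criterion on the pooled success rate (at least 10 of 46) and report the split by arm descriptively. This removes the allocation effect with no change to the randomisation. It is a more lenient rule and does not balance the arms for the neural comparison.

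In either case, state when allocation is made, which scan or scans define success, which children form the denominator and, if the by-arm rule stays, how to classify arms that fall in different bands. Reconcile the 20% threshold with its stated basis of 20 of 50 per group at the same time; if it becomes 40%, the pooled count must be reset to match.

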Participants in the active tDCS group will receive a total of 20 min of stimulation per session, at a maximum of 2 mA intensity. For the sham tDCS control group, the same device, montage, and protocol will be used, but the device will be programmed for the sham condition. This condition delivers 30 s of stimulation (max. 1.0 mA) at the start and end of the session to mimic the sensation of the active condition. This is the proven gold standard for participant blinding and sham-control [41–43]. The first treatment session will ramp up to 1.0 mA for all participants. Participants in the sham tDCS group who tolerate 1.0 mA will remain at 1.0 mA in each treatment session. Participants who do not tolerate 1.0 mA will have the current adjusted to 0.75 mA and 1.0 mA will be attempted again at the next session. For the active tDCS group, if 1.0 mA in the first treatment session is tolerated, the second treatment session will begin at 1.5 mA. If 1.0 mA is not tolerated, the session will start at 1.0 mA. If 1.5 mA is tolerated throughout the second treatment session, the third treatment session will begin at 2.0 mA. If 1.0 mA is tolerated throughout the second treatment session, the third treatment session will begin at 1.5 mA. For the remainder of sessions, the intensity tolerated in the final 10 min of one treatment session will serve as the starting point in the next treatment session. If a participant is not tolerating a certain intensity at any point during treatment, it will be reduced by 0.25–0.5 mA, and their symptoms will be re-evaluated at the reduced intensity and adjusted accordingly.

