#### Safety and tolerability

At T0 and T1, participants complete a baseline and follow-up tDCS tolerability questionnaire, which assesses their experience with the stimulation and their assumption of group membership. At each tDCS session, a full body 16-item systems questionnaire and the NIBS tolerability questionnaire will be completed by the participant and parent to assess the participant’s tolerability of tDCS and to monitor any side effects or adverse events [58–60]. Adverse event (AE) monitoring will begin at the baseline assessment and continue through the study timeline. All AEs will be evaluated by the study physician for seriousness, severity, expectedness, and relatedness to the intervention, using a validated AE worksheet (see Appendix).

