#### Clinical

The CGI severity [65] and improvement assessments include an interview by the physician with the participant and caregiver. Parent-reported measures include the Aberrant Behaviour Checklist (ABC) [66, 67], Emotional Dysregulation Inventory (EDI) [68, 69], Autism Impact Measure (AIM) [70], and Emotional Regulation Checklist (ERC) [71]. These measures have been validated in youth with ASD and will indicate clinical treatment-related improvement. The ABC has excellent reliability and was specifically designed to measure treatment effects on aberrant behaviors, with extensive application in previous ASD trials [72]. The EDI-reactivity scale measures poorly regulated negative emotions, and the EDI-dysphoria scale measures minimal positive affect and motivation. The AIM measures treatment-related improvements in children with ASD across several ASD symptom domains [70]. The ERC measures emotional regulation and is sensitive to a broad range of regulatory processes [73].

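### The stated blinding check asks only participants, so it cannot detect unblinding of the parents and physician who rate the clinical outcomes, although only the active arm is escalated

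*Protocol article*

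**What the plan says.** **Who is blinded.** Randomization and blinding states: "Participants, family members, assessors, and investigators will all be blinded to group allocation". On the mechanism it adds: "The devices will be preprogrammed with codes that correspond to specific stimulation parameters" and "During each session, participants will be provided with a code aligning with their group assignment to maintain blinding".

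**What the arms receive.** Under tDCS intervention, the sham setting is described thus: "This condition delivers 30 s of stimulation (max. 1.0 mA) at the start and end of the session". It then says: "Participants in the sham tDCS group who tolerate 1.0 mA will remain at 1.0 mA in each treatment session". An active participant who tolerates 1.0 mA in session 1 starts session 2 at 1.5 mA and, if that is tolerated, session 3 at 2.0 mA. In either arm the current can be lowered if it is not tolerated.

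**How blinding is checked.** The Feasibility section lists success of blinding among the feasibility measures. It is determined from two questions on the follow-up tolerability questionnaire: which group the respondent thinks they were in, and how sure they are. Safety and tolerability says that participants complete this form, "which assesses their experience with the stimulation and their assumption of group membership".

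**Who rates the outcomes.** In the Clinical section, "Parent-reported measures include the Aberrant Behaviour Checklist (ABC"), followed by EDI, AIM and ERC. The CGI is rated by a physician who interviews the participant and caregiver.

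**The concern.** A blinding check is informative about outcome bias when it asks the people whose beliefs can move the outcome. Here the named clinical scores are judgements by a parent or a physician, while the guess is collected from the participant. A child may guess no better than chance while the parent who helps at 15 home sessions has formed a firm view.

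The escalation rule is a plausible source of such a view, because a current above 1.0 mA exists in one arm only. If raters became unblinded, expectation could shift the ABC, EDI, AIM, ERC or CGI, and the stated check would still report success. That matters even in a pilot. Success of blinding is one of the things the pilot sets out to establish, and the Discussion relies on double-blinding, with the CGI, to limit placebo effects. An undetected weakness would pass into the full-scale RCT.

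**Working it through.** The plan gives no figure for blinding to reproduce, so the check has three parts.

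**1. Raters against respondents.**

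| Instrument | Rated by | Asked to guess the group, as described? |
|---|---|---|
| ABC, EDI, AIM, ERC | Parent | No |
| CGI severity and improvement | Physician | No |
| Follow-up tolerability questionnaire | Participant | Yes |

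Four of the five instruments are parent-rated and the fifth is physician-rated, so none is rated by the person described as giving the guess. The pool of usable answers may also be reduced: Eligibility sets no IQ cut-off, and Consent provides for failed capacity assessments and non-verbal assent.

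**2. Nominal current by session, from the tDCS intervention rules.**

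| Path | Active | Sham | Sessions that differ |
|---|---|---|---|
| Full tolerance | 1.0, 1.5, then 2.0 mA in sessions 3–15 | 1.0 mA in all 15 | 15 − 1 = 14 |
| 1.0 mA not tolerated in session 1 only, and 1.5 mA held from session 3 (assumed) | 0.75, 1.0, then 1.5 mA in sessions 3–15 | 0.75, then 1.0 mA in sessions 2–15 | 15 − 2 = 13 |

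(For the second path, 0.75 mA in active session 1 is an assumed reduction of 0.25 mA.)

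A setting above 1.0 mA can occur only in the active arm, so whoever sees or sets one knows the allocation. A setting at or below 1.0 mA from session 2 on suggests sham but does not prove it, since an active participant with poor tolerance could be there too.

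**3. Precision of a check by respondent.** The article names no index. Assume Bang's index with every respondent guessing, so that the index is 2p − 1 for a proportion p of correct guesses. At p = 0.5 the 95% half-width is

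1.96 × 2 × √(0.25/n) = 1.96/√n.

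- All randomized, 46/2 = 23 per arm: 1.96/√23 = 0.41.
- After the 10% loss in Sample size, 46 × 0.9 = 41.4, or 20 to 21 per arm: 1.96/√21 = 0.43 and 1.96/√20 = 0.44.

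A half-width of 0.43 to 0.44 on the index is about 21 to 22 percentage points on p. The check can show gross unblinding of parents but not a mild tendency. The formula assumes independent guesses. That is reasonable for parents of different children, but not for one physician who rates many.

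**The case against.** The strongest case on the other side is that the disclosure route is inferred. A reader might conclude that the codes reveal allocation to families, or that the double-blind claim is false. The article does not support either conclusion:

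- It does not say that codes are reused, that they are readable, or that the device displays the current. Issuing a code at every session is compatible with opaque codes that change each time.
- A family sees only its own sequence, and nothing says it is told the escalation rule.
- Setting changes also occur in sham (0.75 mA, then a retry of 1.0 mA), and an active participant can start session 2 unchanged.
- Nothing places the CGI physician in the home sessions, and assessors are stated to be blinded.
- An independent research assistant holds the allocation schedule and could select the codes. Who does so is detail an article may leave to the full protocol.

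All of this stands, and it limits the point to what can be disclosed and to whom.

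It can also be said that the word participants may include caregivers, since the usability section uses it loosely for device users. That is possible. However, Safety and tolerability names participant and parent together for the per-session forms and participants alone for the form with the guess, so the narrower reading is the fair one. On either reading, no guess is described for the physician.

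Finally, the clinical ratings are secondary in a pilot that does not test efficacy, and no progression criterion in Table 1 uses them. This lowers the severity. It does not remove the gap, because success of blinding is itself a listed feasibility measure.

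**Conclusion.** The measurement gap holds. As described, the check draws on participants only, while all five named clinical instruments are rated by a parent or a physician, so it cannot detect unblinding of the outcome raters. The arm-specific escalation makes this more than a formality: under full tolerance the nominal setting differs in 14 of 15 sessions, and any setting above 1.0 mA identifies the active arm to someone who sees or sets it. The most exposed people are session staff and parents who help at sessions. Exposure of the CGI physician is not shown, and actual unblinding of anyone is not shown.

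The conclusion rests on reading participants as the children in the trial. The precision figures also assume 10% loss, a guess from every respondent, and Bang's index. The point is of moderate weight: no efficacy conclusion depends on it, but the pilot could report successful blinding without having examined the raters.

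**What to change.** **Main change.** At T1, once the outcome ratings are complete, put the same two questions (group guess and certainty) separately to the parent who completes ABC, EDI, AIM and ERC and to the CGI physician. Keep the participant's answers. Report correct guesses by arm and respondent with 95% CI. If one physician rates many children, the guesses are clustered, so report them descriptively without the independent-guess interval.

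**Cost.** Two extra questions for two raters. Asking at T1 carries a small risk of prompting raters to think about allocation before T2; placing the questions after the T1 ratings protects T1 but not T2.

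**Secondary safeguard, with delivered current unchanged.** Confirm that codes are uninformative and change at every session in both arms, and that whoever selects codes or adjusts current does not rate outcomes. New codes at each session do not cover reductions made during a session, so the separation of roles is needed as well. This guards against a route the article does not document and does not replace asking the raters.
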